#### 10.1.6. Compensation for Health Injuries

The sponsor and the trial site shall secure measures to fulfill compensation and indemnification obligations for health injuries to subjects, such as obtaining clinical-trial insurance and other necessary actions.

If a subject experiences a health injury as a result of participation in this trial, the trial site shall provide necessary and appropriate medical care and other measures for the injury. For health injuries attributable to this trial, compensation, medical expenses, and medical allowances shall be paid in accordance with the terms of the clinical-trial insurance. However, compensation shall not be provided, in principle, for failure to achieve the expected pharmacologic effect or other benefits of the investigational product.

Health injuries arising from the following reasons shall not be compensated or shall result in a reduction of compensation:

- ✓ When caused by the subject's intentional act or gross negligence.
- ✓ When caused by the principal investigator's or sub-investigator's serious deviation from the clinical-trial protocol, or by the trial site's intentional act or gross negligence.
- ✓ When caused by illegal acts or non-performance of a third party.
- ✓ When caused by chance events (e.g., being struck by a reckless vehicle while traveling to the clinic, food poisoning, etc.).

#### 10.1.7. Strategies for Subject Recruitment

To facilitate broad participant recruitment in this study, for patients residing far from the trial site, the explanation and informed consent procedures described in 10.1.5 will be conducted using an online medical consultation system or similar methods.

#### 10.1.8. Matters Concerning Protection of Subjects' Personal Information

All parties involved in this trial shall give due consideration to the protection of subjects' personal information and privacy in accordance with applicable laws and regulations.

Subjects shall be informed that monitors, auditors, the Institutional Review Board, and regulatory authorities may have access to source documents; such access shall be conducted while preserving the confidentiality of the subjects, and information obtained in this trial shall not be disclosed to third parties except when requested by public authority.

#### 10.1.9. Establishment of Committees

Not applicable.

#### 10.1.10. Data Quality Assurance

##### 10.1.10.1. Trial Site

The principal investigator or sub-investigator shall complete case report forms for all subjects concerning screening, investigational product administration, and subsequent follow-up.

Case report forms for this trial shall be entered into an electronic data capture (EDC) system.

The principal investigator shall verify that the content of the case report forms is appropriate and shall apply an electronic signature.

The trial site shall retain as the case report form the case report form data generated in the EDC system (including the principal investigator's electronically signed records), audit trails, and electronic signature information stored on electronic media capable of long-term preservation. Quality management at the trial site shall be performed in accordance with the site's own regulations.

The head of the trial site and the principal investigator shall provide direct access to all source documents and other trial-related records and shall cooperate during monitoring, auditing, regulatory inspections, and Institutional Review Board inquiries.

##### 10.1.10.2. Monitoring

The monitor shall conduct monitoring in accordance with the trial's "Procedures for Conducting Monitoring" to confirm that the trial is performed in compliance with GCP, the clinical trial protocol, standard operating procedures, and applicable regulations, and that data reliability is adequately ensured.

Monitoring should include on-site direct review, such as source data verification comparing source documents with case report forms, as well as off-site monitoring.

If the monitor identifies any discrepancy between source documents and case report forms, the monitor shall obtain from the principal investigator a record explaining the reason for the discrepancy.

#### 10.1.10.3. Data Management

The data management leader and staff shall implement quality control at each stage of data handling, in accordance with the “Procedures for Data Management Activities,” to ensure the reliability of all trial-related data and its proper processing.

In addition, the procedures for EDC system development, case report form preparation, data review, and data lock shall be carried out in accordance with the Data Management Plan and related documents.

Upon completion of the data management activities, a “Data Management Report” will be prepared.

#### 10.1.10.4. Audit

The auditor shall evaluate, independent of routine monitoring and clinical-trial quality-management activities, that the conduct of the trial, data generation, documentation (recording), and reporting are performed in compliance with GCP, the clinical trial protocol, standard operating procedures, and applicable regulations. The auditor shall conduct the audit from a third-party perspective as part of quality-assurance activities, in accordance with the trial’s “Audit Plan” and the “Standard Operating Procedure for Conducting Audits.”

#### 10.1.10.5. Clinical Trial Coordinator

The Clinical Trial Coordinator shall be responsible for the quality of the trial data; therefore, he/she shall establish the trial’s quality-control standards, implement a quality-management system, and assure quality based on a risk-based approach.

#### 10.1.11. Identification of Source Data\*

- 1) Source documents are evidence that the subject actually exists and that the collected data is complete. Source documents shall be retained at the trial site where the principal investigator is affiliated.
- 2) Data entered in the case report form on the basis of source documents must be consistent with the source documents; any discrepancy must be explained. As needed, the principal investigator or sub-investigator shall request retrieval or provision of prior medical records. In addition, the most recent medical records must be available for review.
- 3) The source documents that constitute the basis for the data are listed below. The trial site

shall prepare a list identifying the source documents.

- ✓ Records of subject consent and information provision to the subject (signed informed consent form, medical information release, etc.)
- ✓ Medical records, sealed charts or worksheets (documents created for this trial and attached to the medical record), nursing records, documents related to case enrollment, and the evaluation, test, and observation records specified in this trial (laboratory data, films, test requisitions), i.e., records that form the basis for CRF completion
- ✓ Records of the treatment administered in this trial (surgical records, etc.)

4) The handling of test and observation records performed at external (partner) sites is described in Appendix 4.

#### 10.1.12. Costs and Conflict of Interest

##### 10.1.12.1. Funding Source and Conflict of Interest

This trial will be conducted using research funding from the Japan Agency for Medical Research and Development (AMED), a national research and development corporation.

Conflicts of interest of individuals involved in this trial, such as the Clinical Trial Coordinator, principal investigator, and sub-investigators, shall be managed appropriately in accordance with the policies of the trial site. The conflict-of-interest status shall also be disclosed to subjects in the explanatory documents.

##### 10.1.12.2. Costs Related to the Clinical Trial

Costs for medical care, surgery, examinations, and hospitalizations required for examinations during the clinical trial period shall be covered by health-insurance benefits. Montepase (recombinant) will be purchased with research funds, and subjects will incur no charge.

##### 10.1.12.3. Payment of Burden-Reduction Allowance

In accordance with the regulations of each trial site, a burden-reduction allowance shall be paid to subjects.

#### 10.1.13. Initiation and Termination of the Trial at the Trial Sites

##### 10.1.13.1. Initiation of the Trial

The date on which the investigational product is first delivered to the initial trial site shall be considered the trial start date.

#### 10.1.13.2. Termination of the Trial at a Trial Site

After all subjects have completed the observations, examinations, and assessments stipulated in this clinical trial protocol, the principal investigator shall report in writing to the head of the trial site that the trial has been completed and provide a summary of the trial results. The head of the trial site shall promptly notify the Institutional Review Board in writing of the trial's termination and based on the report submitted by the principal investigator, shall report a summary of the trial results.

#### 10.1.13.3. Suspension of the Trial

The clinical trial coordinator shall suspend the entire trial under any of the following circumstances:

- 1) When, based on matters concerning the quality, efficacy, or safety of the investigational product, the clinical trial coordinator judges that continuation of the trial is infeasible.
- 2) When, on the basis of the information in 1), the head of the trial site orders suspension.
- 3) When, for any other reason, the clinical trial coordinator determines that the trial should not continue.

If any of the above suspension criteria arise, the clinical trial coordinator and the principal investigator shall immediately confer regarding trial suspension or related actions. Upon making a decision to suspend the trial, the clinical trial coordinator shall promptly inform all trial personnel. The principal investigator shall promptly inform subjects of the suspension and its reasons, and shall ensure the safety of the subjects. The principal investigator shall report the suspension in writing to the head of the trial site, the Institutional Review Board, and the relevant departments of the affiliated medical institution, and shall follow the procedures established by that institution.

#### 10.1.14. Policy Regarding Disclosure

Information on this trial will be made public through registration in the Japan Registry of Clinical Trials (jRCT). The results of this trial belong to Saga University. Publication of the results in conference presentations, journal articles, etc., requires the approval of the clinical trial coordinator. In addition, the data may be provided to pharmaceutical companies or other entities for purposes such as marketing-authorization applications.

#### 10.1.15. Secondary Use of Data

Data collected in this trial may be used for purposes such as submission dossiers to regulatory authorities in Japan and abroad, and for research aimed at elucidating the mechanism of action,

among others. The explanatory document provided to subjects will include and describe, in addition to participation in this trial, the prospective secondary use of data. If consent to this trial is obtained, it shall be deemed that consent for the secondary use of data has also been obtained.

## Appendix 2

### 10.2. Definition, Severity, and Causality of Adverse Events and Serious Adverse Events

#### 10.2.1. Detailed Definition and Explanation of Adverse Events

##### <Definition of Adverse Event>

An adverse event (AE) is any unfavorable and unintended sign (including abnormal clinical laboratory values) that occurs in a subject temporally associated with the use of the investigational product, regardless of whether a causal relationship with the investigational product exists. A “side effect” refers to an AE for which a causal relationship with the investigational product is established. The criteria for causality assessment are described in 10.2.3. Recording and follow-up of Adverse Events and Serious Adverse Events.

##### <Examples Considered as Adverse Events>

- ✓ Abnormalities in clinical laboratory values (hematology, clinical chemistry, urinalysis) or other safety-assessment parameters (including worsening from baseline) that, in the judgment of the principal investigator or sub-investigator based on medical and scientific assessment, are clinically significant (i.e., not related to progression of the underlying disease or represent a deterioration of the subject’s condition beyond what was anticipated). Clinical significance includes:
  - Presence of associated symptoms
  - Requirement for additional investigations, or need for medical or surgical treatment
  - Discontinuation of the trial, or addition of clinically meaningful concomitant medication or other therapy
- ✓ Exacerbation of chronic or intermittent symptoms that were present before trial initiation (including increased frequency and/or severity of symptoms).
- ✓ Newly identified or diagnosed symptoms after the start of investigational product administration (even if the symptom may have existed prior to trial initiation, it is considered an AE if identified or diagnosed after dosing).
- ✓ Signs, symptoms, or sequelae suggestive of a drug-drug interaction.
- ✓ Signs, symptoms, or sequelae suggestive of overdose of the investigational product or concomitant medication. Overdose itself is not reported as an AE or SAE, except that intentional overdose performed with the intent of suicide or self-harm must be reported regardless of the presence of sequelae.

<Examples Not Considered as Adverse Events>

- ✓ Abnormalities in clinical laboratory values or fluctuations in other safety-assessment parameters that are related to the underlying disease, except when the principal investigator or sub-investigator judges that the subject's condition is clinically more severe than expected.
- ✓ Progression of the disease under study and the emergence of new lesions per se are not regarded as AEs. However, worsening of symptoms associated with the underlying disease is treated as an AE.
- ✓ Planned medical or surgical procedures (e.g., endoscopic examinations).
- ✓ Unfavorable medical occurrences that have not manifested (e.g., social or convenience hospitalizations).
- ✓ Variations in diseases or conditions that were confirmed or identified before trial initiation and that fall within the expected daily variability or that have not worsened.
- ✓ The lack of efficacy or the absence of the expected pharmacologic effect is not reported as an AE. These examples are described in the efficacy evaluation.

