#### 2.3.1. Risk Assessment

Adverse events that may occur with administration of monteplase (genetically engineered) include retinal toxicity (retinal morphological changes, etc.), increased sub-macular

hemorrhage, macular hole, vitreous hemorrhage, anterior chamber hemorrhage, endophthalmitis, elevated intra-ocular pressure, retinal detachment, corneal opacity, progression of cataract, etc. In addition to pharmacologic effects of the drug itself, events associated with vitreous surgery or intra-ocular tamponade are also encompassed.

To minimize these risks, the trial sites for this study shall be facilities that have prior experience with sub-retinal administration of tPA preparations, and patients at high risk will be excluded by the exclusion criteria.

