| Evaluation of the efficacy of sub-retinal Monteplase (recombinant) in patients with SMH secondary to AMD or RAM, using ophthalmic examination findings as indices. | <Efficacy Evaluation Items>
1) Change in CFT from baseline at Week 4.
2) Presence or absence of a foveal hemorrhage measuring $\geq 1$ disc diameter at Week 4.
3) BCVA (logMAR equivalent) at Week 4.
4) Change in BCVA (logMAR equivalent) from baseline at Week 4. |

|                                                                                                        |                                                                                                                                                          |
|--------------------------------------------------------------------------------------------------------|----------------------------------------------------------------------------------------------------------------------------------------------------------|
|                                                                                                        | 5) Change in CFT from baseline at Week 12.
6) BCVA (logMAR equivalent) at Week 12.
7) Change in BCVA (logMAR equivalent) from baseline at Week 12. |
| Secondary (safety)                                                                                     |                                                                                                                                                          |
| To evaluate the safety of subretinal administration of montepilase (recombinant) in patients with SMH. | Adverse events                                                                                                                                           |

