#### 8.4.7. Disease-Related Events

Events that may occur in association with the underlying disease or the surgical procedure include pre-retinal hemorrhage, intraretinal hemorrhage, sub-retinal hemorrhage, vitreous hemorrhage, serous retinal detachment, macular edema, re-bleeding, hard exudates, etc. These

events shall be evaluated, in light of the subject's underlying disease condition, for the anticipated intensity, frequency, duration, and any reasonable possibility of association with the trial intervention, to determine their relevance as an AE or SAE and to assess causality with the investigational product.

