#### 9.6. Safety Analyses

For the following items, the number of subjects evaluated, the number of events, and the incidence proportion will be calculated.

- Adverse events, adverse drug reactions
- Serious adverse events, serious adverse drug reactions
- Adverse events resulting in death, adverse drug reactions resulting in death
- Adverse events leading to discontinuation of the trial, adverse drug reactions leading to discontinuation of the trial

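### The rules on whether post-dose bleeding is an adverse event conflict, so sub-macular re-bleeds without recorded symptomatic worsening can be left out of the only safety endpoint

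*Protocol*

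**What the plan says.** Five places in the protocol bear on this.

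- **Section 2.3.1 (Risk Assessment)** lists what may follow the drug: "Adverse events that may occur with administration of monteplase (genetically engineered) include retinal toxicity (retinal morphological changes, etc.), increased sub-macular", where the next word is hemorrhage. Vitreous hemorrhage is in the same list.
- **Section 10.2.1 (definition)** describes an adverse event as "any unfavorable and unintended sign (including abnormal clinical laboratory values) that occurs in a subject temporally associated with the use of the investigational product", and adds that a causal link is not required.
- **Section 10.2.1 (examples not considered adverse events)** says: "Progression of the disease under study and the emergence of new lesions per se are not regarded as AEs". The next sentence takes part of this back: "However, worsening of symptoms associated with the underlying disease is treated as an AE".
- **Section 8.4.7 (Disease-Related Events)** names, among others, "sub-retinal hemorrhage, vitreous hemorrhage, serous retinal detachment, macular edema, re-bleeding, hard exudates, etc". Each is to be weighed against the expected course of the subject's disease and any reasonable possibility of a link with the intervention, "to determine their relevance as an AE or SAE and to assess causality with the investigational product".
- **Sections 3 and 9.6.** The safety objective is "To evaluate the safety of subretinal administration of montepilase (recombinant) in patients with SMH", and adverse events are its only endpoint. The first item tabulated in Section 9.6 is "Adverse events, adverse drug reactions". The others are the serious, fatal and discontinuation subsets. Re-bleeding has no line of its own.

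**The concern.** In a single-arm trial, a safety count is useful only if events enter it by a rule that does not already answer the causal question. Here the condition treated and one of the listed risks of the treatment are the same finding: blood under the macula. If a larger or new bleed after dosing can be set aside as progression, the decision whether it was disease or drug is made before the event is recorded, and the reader of the results never sees it.

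The judgement is made without masking (Section 6.4), at several sites, and with no committee to harmonize it (Section 10.1.9). At stake is the completeness and comparability of bleeding counts in data that, under Section 10.1.14, may be provided for marketing-authorization applications.

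**Working it through.** The plan gives no figure on this point, so the check is mainly of the text against itself.

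**Step 1. Follow one event through the rules.** Take a sub-macular hemorrhage that enlarges after dosing, seen on OCT or at fundus examination, with no recorded worsening of symptoms.

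| Rule | Result for this event |
|---|---|
| 2.3.1 risk list | A possible adverse event of monteplase |
| 10.2.1 definition | An adverse event, whatever the cause |
| 10.2.1 exclusion | Not an adverse event, if read as progression or a new lesion per se |
| 10.2.1 symptom sentence | Does not apply: no worsening of symptoms recorded |
| 8.4.7 | Undecided: investigator's judgement, including possible association |

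The same event is in, out or undecided depending on which passage is applied, and none of them is given precedence.

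**Step 2. Order of the judgements.** The definition asks for recording first and causality afterwards (Section 10.2.3). Section 8.4.7 makes possible association an input to whether the event is recorded at all. That is the point at which attribution can remove an event.

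**Step 3. Routes into the count.**
- Worsening symptoms of the underlying disease count (Section 10.2.1).
- Hospitalization for treatment makes an untoward occurrence serious. Events needing intervention to prevent such outcomes go to a seriousness assessment (Section 10.2.2).
- Section 8.4.7 requires the named bleeding events to be evaluated, not ignored.
- Acuity can still fall measurably from the entry limit. Table 8-1 runs down to 0.001, so from 0.2 the room is −log10(0.001) − (−log10(0.2)) = 3.0 − 0.7 = 2.3 logMAR.

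What remains outside is mainly hemorrhage that appears or grows without recorded symptomatic worsening.

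**Step 4. Other records of bleeding.** Fundus examination notes whether macular hemorrhage is present (Section 8.2.6), and photographs note foveal hemorrhage of at least one disc diameter (Section 8.2.2). Both give presence, not increase. Re-operation for re-bleeding enters the primary analysis as a change of 0, while data after rescue gas injection are excluded (Section 9.3.2). None of these feeds the Section 9.6 tables.

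**Step 5. Illustration of scale.** The protocol says that many patients re-bleed (Section 3, Week 12 rationale) but gives no rate. Assume that all 20 planned subjects are dosed, that subjects are independent, that the true re-bleed probability is p, and that a share q of re-bleeds is classed as progression.

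Expected number counted = 20 × p × (1 − q). Chance of counting at least one = 1 − (1 − p(1 − q))^20.

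| p (assumed) | Expected counted, q = 0 | Chance of at least one, q = 0 | Expected counted, q = 0.5 | Chance of at least one, q = 0.5 |
|---|---|---|---|---|
| 5% | 1 | 64% | 0.5 | 40% |
| 10% | 2 | 88% | 1 | 64% |
| 20% | 4 | 99% | 2 | 88% |
| 30% | 6 | 99.9% | 3 | 96% |

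Neither p nor q comes from the protocol. The table shows how the count responds to them and does not estimate the loss.

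**The case against.** The strongest reply is that the exclusion is narrow. It covers progression and new lesions only per se, the next sentence restores symptomatic worsening, and Section 8.4.7 is the more specific provision, naming re-bleeding and requiring a decision on it. A bleed that costs vision, needs repeat vitrectomy or leads to hospitalization for treatment has a route into the count. Vitreous hemorrhage is not the disease under study: it is graded separately in Table 8-2 and listed as an ocular complication in Table 3-1. Bleeding is also documented elsewhere in the case report form.

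Most of this stands and limits the point. It does not remove it. Section 8.4.7 requires a decision but gives no criterion that two investigators would apply alike, and it mixes attribution into that decision. Documentation elsewhere is not the safety endpoint.

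Two stronger readings are tempting. A reader might infer that re-bleeds could vanish from the safety results altogether. That would require every route in Step 3 to fail for every bleed, which the text does not support. A reader might also infer that the protocol excludes the principal harm of a thrombolytic. Section 2.3.1 does not rank its risks, and it says that events of surgery and tamponade are included in the list.

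**Conclusion.** The point holds as a conflict between passages. Sections 2.3.1, 8.4.7 and 10.2.1, including the definition of an adverse event, do not give one answer for post-dose bleeding. The gap is mainly new or increased sub-macular hemorrhage without recorded symptomatic worsening, plus classification that may vary between sites. The direction is towards under-counting, because the exclusion can only remove events. The size cannot be determined: no re-bleeding rate is stated, and the share that investigators would class as progression is unknown. The conclusion rests on the wording alone and assumes that sites apply Section 10.2.1 as written.

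A related effect depends on interpretation. Section 10.2.3 accepts a causal relationship only if, among other things, comorbidities and medical history did not contribute. If AMD or RAM is read as falling under these, a re-bleed recorded as an adverse event would rarely become an adverse drug reaction. The all-cause count would then be the more informative one, which is a further reason for it to be complete.

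**What to change.** - **Sections 10.2.1 and 8.4.7:** state that re-bleeding, new or increased sub-macular hemorrhage, and the other bleeding events named in Section 8.4.7 are recorded as adverse events whenever they occur or worsen after dosing, regardless of attribution. Causality and seriousness are then assessed separately under Sections 10.2.2 and 10.2.3. Add a cross-reference so that the progression exclusion does not override this.
- **Section 9.6:** tabulate post-dose re-bleeding or hemorrhage increase as its own line, with subjects evaluated, number of events and incidence proportion.
- **Case report form:** say how an increase is to be recognized from the scheduled OCT, photographs and fundus examination, since these now ask only for thickness or for presence. Some judgement will remain, but it will concern whether a bleed occurred and not why.

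The cost is protocol and case report form wording. No visit, procedure or treatment rule changes. Reported event rates will be higher and will include bleeds due to the underlying AMD or RAM, so the report should say that the line is all-cause and has no control group.
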